## Methods and Analysis

### Study Design

The multicenter study “Heartbeat” implement a randomized and controlled pre-post-study design involving two intervention trials with parallel groups, for patients with elective cardiac catheterization and practitioners at the catheterization lab, respectively (Figure 1, DRKS No: 00026624^1^). The patient study with a 1:1 randomization by person and a standard treatment control group involves three measurement points: the day before (M1 = admission day) and the day after the video-based stress management intervention and cardiac catheterization examination (M2 = CC examination day), and 6 months after baseline (M3). The MBSR intervention trail for the practitioners at the CC lab involves a 1:1 randomization by group and a no-treatment control group with three measurement points: before (M1) and after the 8-week (M3) intervention with a mindfulness-based stress reduction program, as well as 6 months after baseline (M3). The study takes place at the two clinic sites of the Ernst-von Bergmann community clinic, in Potsdam (patients and practitioners) and Bad Belzig (only patients). The time of data collection is estimated with ~1 h for all questionnaires and 2 days for the physiological measurements (practitioners). The data collection period is planned from 01/2021 to 12/2022.

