### Participants

All patient with an elective cardiac catheterization, hospitalized in the Ernst-von-Bergmann clinic in Potsdam or Bad Belzig, and all staff members at catheterization lab at the Ernst-von-Bergmann clinic in Potsdam are eligible for participation. Patients between the ages of 30 and 75 years with a scheduled heart catheter examination were recruited for study participation. The following criteria should be met: the CC examination have to be elective and non-acute. In addition, only patients, scheduled for coronary angiography, are included. Exclusion criteria were: the inability to fill in a questionnaire, pregnancy and mental health problems. Only practitioners—physicians or nurses—that work at the catheterization lab are included in the intervention trail. The exclusion criterion for practitioners is the presence of an endocrinological metabolic disease. All participants have to sign informed consent after receiving written and verbal information. The study is conducted according to the Declaration of Helsinki (ethics approval 03/06/2021, ethics review board University of Potsdam No. 38/2021) and complied with the Consolidated Standards of Reporting Trials (CONSORT).

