### Sample Size Determination

We calculated the sample size for two patient groups for two measurement points based on a pilot study. The sample was powered to assume a medium effect size (*d* = 0.25) and a minimum detectable clinical difference of 0.5 standard deviation on the (z-standardized) main criterion: perceived stress. For the main criterion, the power for significant group differences is 1-β = 0.93 with a case number of *N* = 60 people per group (38). As the sample for the practitioners was limited to all members of the catheterization lab of the clinic who fulfill the inclusion criteria, a sample size determination was not required.

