### Randomization Procedure and Blinding

The process of randomization to the allocation arm was performed prior to recruitment via a randomization list. This randomization list was generated via the computerized randomization tool Research Randomizer (https://www.randomizer.org/). Participants will be randomly assigned to either the intervention or control condition according to the randomization list. Patients and practitioners cannot be blinded due to their active role in the intervention. Practitioners at the cardiac catheterization laboratory are blinded to the group allocation of the patients.

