### Statistical Analysis

All statistical analyses will be performed using SPSS. The data of the practitioners will be mainly analyzed descriptively due to the small sample size. Interferential statistics will be used to identify group differences. A comparison with norms of the German general population will be performed to assess the stress of the practitioners in the cardiac catheter laboratory. Baseline and post-interventional physiological data like circadian profile slopes of HRV and derived indicators (SDNN, RMSSD, number and percentage of R-R intervals lower or >50 msec) as well as saliva cortisol, alpha-amylase and lysozyme measurements will be compared on an intraindividual level. The data of the patients will be analyzed according to a multivariate variance analysis (between-subject factor: intervention group vs. control group). Sociodemographic data, sedative medication, adherence to the intervention will be implemented as control variables or stratification variables for subgroup analysis. Statistical significance is set at *p* < 0.05 (two-sided) and effect sizes will be reported.

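### The practitioners' unit of randomisation is described in two ways that do not fit together, and the planned between-arm tests make no allowance for group allocation

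*Protocol article*

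**What the plan says.** The Study Design section describes the two trials one after the other and gives each its own unit of allocation. For patients: "The patient study with a 1:1 randomization by person and a standard treatment control group". For practitioners, the trial "involves a 1:1 randomization by group and a no-treatment control group".

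The section Randomization Procedure and Blinding gives a single procedure, based on a computer-generated list drawn up before recruitment: "Participants will be randomly assigned to either the intervention or control condition according to the randomization list". It covers both trials, since it goes on to say "Patients and practitioners cannot be blinded due to their active role in the intervention". It names no group unit and no separate scheme for practitioners.

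Practitioners come from one place. Under Participants, "all staff members at catheterization lab at the Ernst-von-Bergmann clinic in Potsdam are eligible for participation". Their number is not given; the Sample Size Determination section says that for them "a sample size determination was not required".

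The Statistical Analysis section makes the practitioner analysis chiefly descriptive because the sample is small, but adds "Interferential statistics will be used to identify group differences" (read here as inferential statistics) and sets a two-sided 5% significance level. The Abstract goes further and says that intervention effects in practitioners, as in patients, will be evaluated by multivariate variance analysis. Neither place mentions a group factor or any allowance for clustering.

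**The concern.** The unit of randomisation decides which variation the arm difference must be judged against. If individuals were allocated, variation between individuals is the right yardstick. If whole groups were allocated, the yardstick is variation between groups, and a person-level test that ignores this understates the error whenever members of a group resemble each other. That is plausible for stress scores among colleagues who share a workplace.

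Within a single laboratory only a few groups can be formed, possibly one per arm. In that case any difference between the two groups that has nothing to do with the mindfulness programme would appear as a programme effect, and no analysis could separate the two. The comparison concerned includes perceived and chronic stress, the practitioners' primary outcomes. As the article stands, a reader cannot tell whether a practitioner p-value means what it claims.

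**Working it through.** **Side by side.** Study Design contrasts "1:1 randomization by person" (patients) with allocation by group (practitioners). The randomisation section has participants assigned from a list, for both trials, with no group unit. The analysis passages plan between-arm inference with no group term. The analysis therefore fits individual allocation and does not fit the wording in Study Design.

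**No figure to reproduce.** The article gives no practitioner sample size, power or number of groups. The calculation below is an illustration only.

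**Inputs.** From the article: significance level 0.05, two-sided. Assumed, because the article does not give them: m staff per group, k groups per arm, and intraclass correlation ICC (the share of outcome variance that lies between groups). A person-level two-sample t-test stands in for the planned comparison, because the article names no specific test for practitioners beyond the Abstract's variance analysis.

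**One group per arm (k = 1).** With between-group variance B and within-group variance W:

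- true variance of the arm difference: 2(B + W/m)
- variance the person-level test estimates: 2W/m
- ratio: R = 1 + m·B/W = 1 + m·ICC/(1 − ICC)
- true type I error: 2·P(T > t_crit/√R), with T on 2m − 2 degrees of freedom

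For m = 10, t_crit = 2.101 on 18 degrees of freedom:

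- ICC 0.02: R = 1 + 0.2/0.98 = 1.204; 2.101/1.097 = 1.915; error 7.2%
- ICC 0.05: R = 1 + 0.5/0.95 = 1.526; 2.101/1.235 = 1.701; error 10.6%
- ICC 0.10: R = 1 + 1/0.90 = 2.111; 2.101/1.453 = 1.446; error 16.5%

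For m = 15 the same formula gives 8.4%, 13.7% and 22.0%.

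**Check by simulation** (40,000 replicates, no treatment effect), true type I error of the nominal 5% test:

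| Groups per arm × size | ICC 0 | ICC 0.02 | ICC 0.05 | ICC 0.10 | ICC 0.20 |
|---|---|---|---|---|---|
| 1 × 5 | 4.9% | 5.8% | 7.2% | 10.0% | 16.4% |
| 1 × 10 | 5.1% | 7.4% | 10.7% | 16.7% | 27.7% |
| 1 × 15 | 5.0% | 8.4% | 13.8% | 22.0% | 35.7% |
| 2 × 5 | 5.0% | 5.9% | 7.5% | 10.1% | 15.5% |
| 2 × 10 | 5.2% | 7.5% | 10.9% | 16.5% | 26.3% |
| 3 × 10 | 4.9% | 7.0% | 10.4% | 16.0% | 25.3% |

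Formula and simulation agree.

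**Is a valid test available?** With k groups per arm, a group-level comparison has 2(k − 1) error degrees of freedom: 0 for one group per arm, 2 for two, 4 for three. With one group per arm no valid test exists. With two or three, one exists but has few degrees of freedom, and a person-level test does not use it.

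**The case against.** The other side has several good points.

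- The randomisation section never says that assignment is individual. A list can hold groups as well as persons, so a reader who infers a flat logical contradiction goes too far. Individual assignment is the natural reading, but it remains an inference. This stands.
- Allocation by group may be loose wording for delivery in a group, since the Discussion calls the mindfulness programme a group programme. This is possible. The direct contrast with allocation by person, in adjacent sentences, speaks against it, and if it is what was meant, the sentence is misworded and still needs correcting.
- A reader might infer that the practitioner comparison has no valid error term at all. That holds only with exactly one group per arm, and the article gives no number of groups.
- The size of the inflation rests wholly on assumed group sizes and correlations. This stands, and with zero correlation there is none.
- The practitioner analysis is already chiefly descriptive, with comparisons against population norms and within persons. This limits the damage but does not remove it: inferential comparisons are still announced, and the Abstract states a variance analysis without that restriction.
- A condensed article may leave the make-up of groups to a fuller document. That is true of such detail, but here the unit itself is stated, and it does not fit the allocation procedure or the analysis as described.

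**Conclusion.** The point holds in conditional form. The article's stated unit of allocation for practitioners does not match its list-based procedure as naturally read, and it does not match the planned between-arm inference, which makes no allowance for groups.

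If groups were allocated, person-level p-values would be too small whenever outcomes correlate within groups. Assuming one group of 10 per arm and an ICC of 0.02 to 0.10, the true error of a nominal 5% test is about 7% to 17%. With one group per arm the effect is also fully confounded with group, and no adjustment can rescue it. If individuals were allocated, this particular error does not arise.

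A reader might conclude that the practitioner trial was cluster-randomised and that its tests are invalid. The article does not establish that; it leaves open which kind of allocation took place. The patient trial is not affected.

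**What to change.** State once, in both Study Design and Randomization Procedure and Blinding, the unit by which practitioners were actually allocated, and match the analysis to it.

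- **If allocation was individual:** correct the wording in Study Design and say that the mindfulness programme is delivered in a group. Add that shared sessions may still correlate outcomes within the intervention arm. The cost is a few words.
- **If allocation was by group:** give the number and make-up of the groups. With one group per arm, drop the between-arm p-values and report the comparison descriptively. With several groups, either analyse at group level and accept the few degrees of freedom, or report descriptively. The cost is some or all of the practitioner p-values, in an analysis already meant to be chiefly descriptive.

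In either case, bring the Abstract's statement on the practitioner analysis into line with the Statistical Analysis section. No change to the allocation itself is proposed: the list was generated before recruitment, and Study Status reports that the first participants are already recruited.

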Although there is still only limited research on stress-reducing interventions in catheterization labs, a few studies on psychological preparation and video-based psycho-educative interventions in patients have shown beneficial results concerning pre- and perioperative distress, anxiety and coping as well as postoperative recovery and wellbeing (34–37). Less stressed and anxious patients may lead to less complications and reduced durations of cardiac catheterizations that could be beneficial for both patients and practitioners. A lower risk of complications and well-prepared patients may reduce the distress and pressure on the staff at the catheterization lab that in turn could be beneficial for patient safety and therapeutic outcome. To the best of our knowledge, there is no study protocol or study on stress-management in clinical settings that address both group—practitioners and patients—simultaneous. We expect a positive, bidirectional influence from both interventions to both intervention groups.

The objective of the study is to develop and implement an intervention for both practitioners and patients that aims to reduce the physical and psychological strain of a cardiac catheterization. This study tries to answer the following research questions:

Whether and to what extent are cardiac catheterization interventions physically and psychological stressful for both patients and practitioners?Whether and to what extent does a standardized video-based patient education lead to less stress, anxiety, surgical complications, postoperative hospitalization, as well as better recovery, compliance and well-being?Whether and to what extent can practitioners benefit from operational guidelines at the catheterization lab and a stress management intervention in terms of reduced stress during work at the catheterization lab and a faster recovery after a workday?

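### Site is missing from the stated patient model although patients come from two hospitals and the staff programme runs in only one: a modest, nearly free gain in precision, not a demonstrated error

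*Protocol article*

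**What the plan says.** - **Two patient sites, one with the staff trial.** Study Design locates the study "in Potsdam (patients and practitioners) and Bad Belzig (only patients"). The Participants section agrees: patients at either hospital are eligible, but only catheterization-lab staff in Potsdam.
- **Expected spill-over.** The Introduction states: "We expect a positive, bidirectional influence from both interventions to both intervention groups".
- **Allocation.** Patients have a "1:1 randomization by person" (Study Design). On the list, Randomization Procedure and Blinding says "This randomization list was generated via the computerized randomization tool Research Randomizer" and "Participants will be randomly assigned to either the intervention or control condition according to the randomization list". It does not mention strata.
- **Patient model.** Statistical Analysis specifies a "multivariate variance analysis (between-subject factor: intervention group vs. control group"). On covariates it says: "Sociodemographic data, sedative medication, adherence to the intervention will be implemented as control variables or stratification variables for subgroup analysis". Site is not named there. Nor is it among the six sociodemographic items in Table 1, which run from sex and age to income.

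**The concern.** The two sites differ by design in a feature that the authors themselves expect to matter to patients. Site is fixed before allocation and known for everyone, which makes it a safe covariate. The stated covariate list nevertheless leaves it out, while including two variables (sedative medication and adherence) that arise after allocation.

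If patients at the two hospitals differ in stress, mood, strain or sedation, that difference stays in the residual of the stated model. What is at stake is the precision of the estimated video effect and, under a site-stratified list, a test that is stricter than its nominal level.

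**Working it through.** The article gives no figure on site: no site shares and no outcome levels by site. Every site input below is therefore an assumption, and ranges are shown.

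**Inputs.** From Sample Size Determination: n = 60 per group, and a difference of 0.5 SD on perceived stress. From Statistical Analysis: two-sided 0.05. Assumed: share q of patients in Bad Belzig, and site difference D in units of the within-site SD.

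**1. Variance explained by site.** R² = q(1−q)D² / (1 + q(1−q)D²).
- q = 0.2, D = 0.3: 0.0144/1.0144 = 0.014.
- q = 0.4, D = 0.8: 0.1536/1.1536 = 0.133.

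**2. Standard error.** With site in the model, SE = √(2/60) = 0.183 SD. Without it, SE is multiplied by √(1 + q(1−q)D²).
- q = 0.2, D = 0.3: √1.0144 = 1.007, SE 0.184 (0.7% larger).
- q = 0.4, D = 0.8: √1.1536 = 1.074, SE 0.196 (about 7% larger).

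**3. Chance imbalance is the same cost, not a second one.** Under an unstratified list, the difference in site share between arms has SD √(2q(1−q)/60) = 0.073 to 0.089. Multiplied by D, it shifts the estimate with SD 0.022 to 0.072. The square of that shift SD is (2/60)·q(1−q)D², exactly the extra variance in step 2. The ordinary standard error already includes it.

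**4. Power for a 0.5 SD effect.** Power ≈ Φ(0.5/SE − 1.96).

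| q | D | Power without site |
|---|---|---|
| 0.2 | 0.3 | 0.776 |
| 0.4 | 0.8 | 0.722 |
| 0.3 | 0.5 | 0.761 |
| 0.5 | 0.5 | 0.757 |
| 0.5 | 1.0 | 0.688 |

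With site in the model, power is 0.782. Over q = 0.1 to 0.5, the loss is 0.1 to 2.5 points for D from 0.2 to 0.5. It reaches 9.4 points only at D = 1.0 with equal site shares. These figures are for a simple two-group comparison and serve only to compare the model with and without site. The article's stated power of 0.93 is not reproduced by that comparison. That is a separate matter and does not bear on site.

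**5. Type I error without site in the model** (40,000 simulated trials per case).
- Unstratified list: 0.051 (q = 0.3, D = 0.5) and 0.051 (q = 0.5, D = 1.0). The level is held.
- List stratified by site: 0.046 and 0.028. The test is conservative, because stratification removes site variance from the estimate but the unadjusted standard error still counts it. As a check, for q = 0.5 and D = 1.0 the effective critical value is 1.96 × √1.25 = 2.19, with a two-sided tail of 0.028.

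**The case against.** **A condensed article may leave site adjustment to the full protocol or analysis plan.** This has force. The Statistical Analysis section is short and does not call its covariate list complete. Still, it does state a model and name its covariates, so proposing one more pre-allocation covariate is a comment on what is stated. The objection limits the weight of the point rather than removing it.

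**No difference between sites is documented.** This stands. The sites belong to one clinic network, Experimental Procedure/Intervention describes a single sedation policy without distinction by site, and no outcome is reported by site. A reader might infer that outcomes are known to depend on site; the article supports only the conditional statement. The expected spill-over is the best support, but it would reach both patient arms in Potsdam alike. A site term would also miss any change within Potsdam before and after the staff programme.

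**Stronger readings that the article does not support:**
- *That the video effect is biased or false positives are inflated.* Individual 1:1 randomisation rules out systematic bias from omitting site, and the simulation shows the level is held.
- *That there is one list, unstratified by site.* The text neither states nor excludes stratification. The same sentences cover both trials, which are randomised differently, so the singular shows little.
- *That site differences in sedation simply remain in the error.* Sedative medication is a named control variable, so this applies only where sedation is itself the outcome. Its double role as primary outcome and covariate is a separate issue.

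**The pre-post design reduces the cost.** Also true. Table 1 gives M1 values for perceived stress, mood and physiological measures. If these are used as change or adjusted for, stable site differences in level largely drop out. Sedation and complications during the procedure have no such baseline.

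**Conclusion.** The point holds as a modest, optional improvement to a stated model. There are two patient sites, the staff programme runs only in Potsdam, and the named factor and covariates omit site. The consequence is conditional on outcomes differing by site and is confined to precision: a standard error about 0.7% to 7% larger for a Bad Belzig share of 20% to 40% and a site difference of 0.3 to 0.8 SD, and less after baseline adjustment. If allocation was stratified by site, the unadjusted test is conservative instead. Site shares, site differences and the form of the list are all unknown from the article.

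**What to change.** 1. In Statistical Analysis, add site (Potsdam, Bad Belzig) as a fixed factor in the patient models, including the model for sedation as an outcome where counts allow. Cost: one degree of freedom and one line of text.
2. In Randomization Procedure and Blinding, state whether patient allocation was stratified by site. Cost: one sentence.
3. Leave the allocation list as it is. It was generated before recruitment, and Study Status reports that first participants are already recruited, so separate lists per site would now be a mid-trial change in allocation.
4. Do not require stratification by site for complications. The article describes them as rare, and splitting about 120 patients by arm and site could leave sparse cells.

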**Figure 1 F1:**
[figure not shown]
Randomized controlled intervention trials with parallel groups and three measurement points (before and after intervention, 6 months after baseline) for patients with elective cardiac catheterization and practitioners at the catheterization lab (before and after intervention, 6 months after baseline).

